### Interventions

2.4

The study design will be described as a two-center, randomized, location study of probiotics in affiliated hospital of Hubei university for nationalities and its effect on AR symptoms. Probiotic treatment will be compared to the placebo application model, and we will provide probiotics to all patients for another 4 weeks after the trial phase.

Probiotic treatment will be performed by Bifidobacterium triplex. Probiotics are provided in drops. The placebo treatment consisted of dropping carrier solutions containing probiotic treatments (lactose monohydrate, glucose monohydrate), but was no different in color, smell, or taste from probiotics.

### Data collection: quality management and storage

2.5

Reservations will be made at the end of the first meeting for the following dates to facilitate participants’ reservations. Data from each measurement will be collected in writing at a face-to-face meeting and then recorded electronically at the Minda Hospital of Hubei Minzu University. Once recorded, the data is locked to prevent changes. Data lost because it did not appear will be encoded as incomplete. Then, SPSS vision. 25 will be used to analyze the result data. All data collected on the paper will be tagged with a research identification number to prevent identification of participants and stored in a locked cabinet. Only the author of the research report can access these identified data sets.

### Measurement of outcomes

2.6

Tools to measure primary indicators include the following:

(1)The health-related quality of life by means of diaries.(2)In this study, RQLQ will be used to evaluate the comfort level of the 2 groups of patients.(3)CSMS will be used to evaluate allergy symptoms.

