**Methods/Design::**

60 infants and young children with AR were randomly divided into 2 groups: probiotics/placebo group. The main outcome was the use of a comprehensive symptom drug score to assess allergy symptoms. In addition, health-related quality of life was investigated (rhinitis quality of life questionnaire). Secondary outcomes included a visual analog scale of allergy burden and a second quality of life questionnaire. This report describes the study design of a randomized controlled trial.

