### Statistical analysis

2.8

Statistical analyses will be implemented by SPSS 17.0 and Microsoft Excel 2007 software. Data will be represented as mean ± standard deviation (SD). A *t*-test will be performed to compare the changes in measures within groups. Statistical significance will be considered at *P* < .05.

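### The abstract names one main outcome (the symptom and medication score), but section 2.6 lists three unranked primary indicators, so the article conflicts on which outcome decides the trial

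*Protocol article*

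**What the plan says.** The abstract (Methods/Design) speaks of one outcome, in the singular: "The main outcome was the use of a comprehensive symptom drug score to assess allergy symptoms". The next sentence brings in RQLQ without calling it main or secondary: "In addition, health-related quality of life was investigated (rhinitis quality of life questionnaire". A third sentence gives the secondary tier: "Secondary outcomes included a visual analog scale of allergy burden and a second quality of life questionnaire".

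Section 2.6 (Measurement of outcomes) opens with "Tools to measure primary indicators include the following" and numbers three items:

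1. "The health-related quality of life by means of diaries"
2. "RQLQ will be used to evaluate the comfort level of the 2 groups of patients"
3. "CSMS will be used to evaluate allergy symptoms"

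No item is marked as leading, and CSMS comes last. Section 2.2 (Study method) also names the three together without ranking them.

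Section 2.8 (Statistical analysis) has one general threshold: "Statistical significance will be considered at" P < .05. It gives no order of testing and does not say which measure the conclusion rests on.

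**The concern.** The primary outcome fixes what a positive trial means. A reader of the abstract expects the conclusion to rest on CSMS. A reader of section 2.6 finds three measures of equal standing. If CSMS shows no difference and RQLQ does, the abstract's version makes the trial negative, while section 2.6 leaves room to call it positive. The choice between the two could then be made after the data are seen.

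The error rate is also at stake. A 5% threshold gives a 5% false-positive rate for the trial's conclusion only if one pre-named test carries that conclusion. With 60 children and several related scales, a chance difference on one of them is a realistic prospect.

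**Working it through.** **Step 1. Set the statements side by side.**

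| Measure | Abstract | Section 2.6 |
|---|---|---|
| CSMS | the main outcome | primary indicator, third in the list |
| RQLQ | an addition, no rank | primary indicator, second in the list |
| Diary quality of life | not mentioned | primary indicator, first in the list |

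I take the abstract's symptom drug score to be CSMS, since sections 2.2 and 2.6 give CSMS as the tool for allergy symptoms. The two places agree that CSMS is primary. They disagree on whether it is alone.

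**Step 2. Is there a figure to reproduce?** No. The article states no familywise error rate and no power calculation. The only stated figure is P < .05 in section 2.8.

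**Step 3. Error rate if the section 2.6 list is used.** Assumptions, none of them stated in the article: one between-group test per measure, two-sided 0.05, no adjustment elsewhere, and no true effect on any measure.

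Independent tests, 1 − (1 − 0.05)^k:

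- k = 3: 1 − 0.95³ = 1 − 0.8574 = 0.1426, or 14.3%. The upper bound under any dependence is 3 × 0.05 = 15%.
- k = 2 (diary taken as a collection method only): 1 − 0.95² = 1 − 0.9025 = 0.0975, or 9.8%.

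The measures come from the same children and will be correlated, but the article gives no correlations, so a range is needed. For equicorrelated normal test statistics with common correlation ρ, the chance that at least one exceeds 1.96 in absolute value is:

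| ρ (assumed) | three primaries | two primaries |
|---|---|---|
| 0 | 14.3% | 9.8% |
| 0.5 | 12.5% | 9.1% |
| 0.7 | 10.9% | 8.3% |
| 0.9 | 8.4% | 7.0% |

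Every entry is above 5%.

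**Step 4. Error rate after the change.** With CSMS as the single primary at 0.05, the rate is 5%. With three primaries kept and Bonferroni levels of 0.05/3 = 0.0167, it is 1 − (1 − 0.0167)³ = 4.9% if independent, and at most 5% otherwise. Holm has the same 5% ceiling.

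**Step 5. Price of keeping three primaries.** Assume 30 per arm (60 in total; the allocation ratio is not stated), a between-group comparison and 80% power. The detectable standardised difference is (z for α/2 + z for power) × √(2/30), and √(2/30) = 0.258:

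- α = 0.05: (1.960 + 0.842) × 0.258 = 0.72 SD
- α = 0.0167 (Bonferroni, and Holm's first step): (2.394 + 0.842) × 0.258 = 0.84 SD

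**The case against.** The strongest reply is that the conflict is small and the error-rate argument rests on silence.

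- **Rank of RQLQ.** The abstract places RQLQ before its secondary list and calls the other questionnaire a second one, so CSMS and RQLQ could both be meant to stand above the secondaries. This stands in part: the abstract's rank for RQLQ is unclear. Only CSMS is called the main outcome, though, and section 2.6 still differs.
- **The diary.** It may be how data are collected and not a third endpoint, since no instrument or score is named for it. That is a fair reading, and it is why the two-measure figures are given. It does not settle which of CSMS and RQLQ decides.
- **Adjustment.** A reader might infer that the trial may claim success on whichever measure reaches P < .05, with no error control. The article does not say this. Section 2.8 gives a general threshold; it states no success rule and does not rule out an adjustment, which a condensed article may leave to an analysis plan that is not shown. That silence is not a fault in itself. An unseen plan could supply an adjustment, but it could not make the abstract and section 2.6 agree.
- **Other measures.** A reader might count all five named measures towards the error rate, or fault section 2.6 for leaving out the visual analog scale and the second questionnaire. Neither is supported. The abstract labels those two as secondary, so they cannot decide the trial, and section 2.6 is introduced as a list for primary indicators.
- **The test itself.** Section 2.8 describes a t-test of changes within groups, while the rates above assume a between-group test. This is correct, so the figures are conditional and are not the error rate of the analysis as written. The within-group wording is a separate matter.

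**Conclusion.** The concern holds as a conflict between two current statements: one main outcome in the abstract, three unranked primary indicators in section 2.6, and a single threshold in section 2.8 that does not choose between them. Confidence in that conflict is high, and it should be resolved before any unblinded results are seen.

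The size of the consequence is conditional. Used as a list of primaries without adjustment, section 2.6 would raise the false-positive rate from 5% to between 8.4% (correlation 0.9) and 14.3% (independence) for three measures, or between 7.0% and 9.8% for two. The correlations are assumed, and so are between-group testing, two-sidedness and the absence of an adjustment elsewhere. The article does not support going further and saying that the sponsor has planned to accept any one significant measure.

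**What to change.** State in both the abstract and section 2.6 that the between-group comparison of CSMS at the end of the blinded phase is the single primary outcome, and in section 2.8 that it is tested at two-sided 0.05. The end of the blinded phase is the natural point because section 2.4 gives probiotics to all patients for a further 4 weeks afterwards. List RQLQ and any diary quality-of-life measure as secondary. State whether the diary is an endpoint in its own right or only a way of collecting data.

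If the sponsor prefers several primaries, both places should say so, name them, and apply Holm's procedure.

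The cost of the first option is a few sentences and a check that the registry entry matches. The sponsor gives up stand-alone confirmatory claims on RQLQ and the diary measure. The cost of the second is power: under the assumptions in the working, the difference detectable at the first Holm step with three primaries rises from 0.72 to 0.84 SD.

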### Blinding and random

2.7

After completing the first evaluation (the first interview), the research assistant opened an opaque envelope to determine that the participants were randomly assigned to two groups. Randomization is based on a computer-generated sequence of random Numbers built by an independent investigator. These researchers will be independent of the study members responsible for recruiting participants. All outcome measurements will be performed by blind experimenters.

### Statistical analysis

2.8

Statistical analyses will be implemented by SPSS 17.0 and Microsoft Excel 2007 software. Data will be represented as mean ± standard deviation (SD). A *t*-test will be performed to compare the changes in measures within groups. Statistical significance will be considered at *P* < .05.

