Prebiotics are defined by Gibson and Roberfroid, first proposed in 1995: Prebiotics are undigested or indigestible food ingredients that contribute to host health by selectively stimulating bacterial proliferation and/or activity in the colon. Some studies have found that breastfeeding within 6 months after birth is a protective factor for AR in infants and young children, and Odijk et al^[6]^ found that breastfeeding for more than 3 months can effectively reduce the probability of infants suffering from ectopic dermatitis and laryngeal wheezing, especially for those infants and young children with a family history of allergies. One of the reasons that breast-fed infants are less susceptible to allergic diseases than artificially fed infants is the presence of beneficial oligosaccharides in breast milk. Bifidobacteria dominated the intestinal flora of breast-fed infants at 6 to 7 days, while the number of bifidobacteria in the intestinal flora of artificially fed infants was small and the bacterial species was diverse. In present study, we aim to conduct a double-blind randomized controlled trial study to explore the effect of probiotics on AR in infants and young children.

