### Study method

2.2

A total of 60 patients with AR in Otorhinolaryngology-Head and Neck Surgery, Minda Hospital of Hubei Minzu University and West China Hospital of Sichuan University from May 2020 to April 2022 will be selected and randomly divided into probiotic/placebo group according to the numerical table. The study divided the patients into two groups. Patients will be divided into a double-blind probiotic/placebo study, we will assess allergy Symptoms using health-related quality of life by means of diaries, quality of life problems (RQLQ), and Combined Symptoms and Medication Score (CSMS). CSMS is a simple and standardized way to balance symptoms with the need for antidepressants. RQLQ is a disease-specific indicator used to assess health-related quality of life, including the patient's physical, social and emotional health.

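### The one test named in section 2.8 looks at change within each group, so as worded it does not compare probiotic with placebo and contradicts section 2.4

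*Protocol article*

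**What the plan says.** The Introduction describes a controlled trial: "we aim to conduct a double-blind randomized controlled trial study to explore the effect of probiotics on AR in infants and young children". The abstract says that "60 infants and young children with AR were randomly divided into 2 groups: probiotics/placebo group". Section 2.4 (Interventions) gives the contrast of interest: "Probiotic treatment will be compared to the placebo application model".

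The abstract makes a combined symptom and medication score the main outcome. I read this as the CSMS, of which section 2.6 says "CSMS will be used to evaluate allergy symptoms".

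Section 2.8 (Statistical analysis) is four sentences long. It names the software, says that data are shown as mean and SD, states that a t-test "will be performed to compare the changes in measures within groups", and sets the threshold at P < .05. The article states no between-group test, model or treatment-difference estimate anywhere.

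**The concern.** The design asks whether children given probiotic do better than children given placebo. A t-test of change within a group asks whether that group's mean moved from its starting value. Only the first question uses the randomisation.

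Movement shared by both arms is plausible here. Children enter with sensitisation to airborne allergens (section 2.3) over a window from May 2020 to April 2022 (section 2.2), so exposure can differ between a child's first and later assessments. Regression to the mean and placebo response push in the same direction. Any of these can make the probiotic arm's before/after test significant with no probiotic effect. If that result were then read as efficacy, the 5% level would not protect the conclusion.

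**Working it through.** The article gives no power, effect size, SD or dropout figure, so there is no stated calculation to reproduce. The check asks how the test behaves as worded when the probiotic does nothing.

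**Inputs**
- Total of 60 children: abstract and sections 2.2 and 2.3.
- Significance level 0.05: section 2.8. Sidedness is not stated; two-sided is assumed.
- Allocation: section 2.2 says only that "The study divided the patients into two groups". A 30:30 split is assumed.
- Shared mean improvement d, in SD of the change score: not in the article, so a range is shown.
- True treatment effect: zero.

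**Step 1. Within-group test.** With n = 30, the one-sample t statistic on change has 29 degrees of freedom and noncentrality d × √30. At d = 0.5 this is 0.5 × 5.477 = 2.74. The probability p of a significant improvement is the chance that this noncentral t exceeds the upper 2.5% point of t with 29 degrees of freedom.

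**Step 2. Significant in probiotic but not in placebo.** The arms are independent with the same d, so the probability is p(1 − p). At d = 0.3: 0.355 × 0.645 = 0.229.

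| Shared change d (SD of change) | Probiotic arm significant, p | Probiotic significant, placebo not, p(1 − p) |
|---|---|---|
| 0 | 2.5% (5% counting both directions) | 2.4% |
| 0.2 | 18% | 15% |
| 0.3 | 36% | 23% |
| 0.4 | 56% | 25% |
| 0.5 | 75% | 19% |
| 0.6 | 89% | 10% |
| 0.8 | 99% | 1% |

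The last column cannot exceed 25%, reached when p = 0.5.

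**Step 3. Between-group test.** A two-sample t-test on change, 30 against 30, was simulated 100,000 times with no treatment effect. It rejected in 5.1% of trials at d = 0 and 5.0% at d = 0.5. The shared change cancels.

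**Step 4. Change score or ANCOVA.** With equal variances at baseline and follow-up and correlation r between them, the variance of change is proportional to 2(1 − r) and the ANCOVA residual variance to 1 − r². The ratio of ANCOVA to change score is (1 − r²) / [2(1 − r)] = (1 + r)/2: 0.75 at r = 0.5 and 0.90 at r = 0.8. The article gives no r, so the gain is not known.

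**The case against.** The best defence is that the sentence is a language slip. It speaks of comparing changes, which could mean comparing each arm's within-group change, that is, a two-sample t-test on change scores. The article's English is loose elsewhere: section 2.2 describes the medication side of an allergy score as antidepressants. Section 2.4 shows that a comparison with placebo is intended. The article also condenses fuller documents that are not shown.

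Part of this stands: the intent is probably right. It does not rescue the sentence. Its natural meaning is a before/after test in each arm, and this is a test stated wrongly, not a detail left to an analysis plan. A plan that followed it would inherit the error, and one that departed from it would contradict the published text.

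A reader might infer more than the documents support:
- **That the trial will claim efficacy from significance in the probiotic arm alone, or in that arm and not in placebo.** No such decision rule is stated. The percentages in the table are the test's power to detect a real shared change. They become error rates only if the result is read as a treatment effect.
- **That baseline is ignored.** A change score uses baseline by construction; it is only not used as a covariate.
- **That children without follow-up are dropped.** Section 2.5 says "Data lost because it did not appear will be encoded as incomplete", which is a coding rule. No exclusion rule is given, and missing-data handling may properly sit in the analysis plan.
- **That omitting centre is an error.** Adjustment for centre may also be left to the analysis plan.

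**Conclusion.** The point holds in this form: the only inferential test in the article does not, as worded, compare probiotic with placebo, and it contradicts section 2.4 and the randomised, placebo-controlled design. It must be corrected, because the stated test cannot answer the trial's question.

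The table sizes the problem: across shared improvements of 0.2 to 0.8 SD, the probiotic arm's own test is significant in about 18% to 99% of trials with no treatment effect, and probiotic-only significance ranges from about 1% to 25%. These figures rest on 30 per arm, two-sided testing and an assumed shared change. The direction does not: any improvement common to both arms raises the within-group rate and leaves the between-group rate at about 5%.

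The advantage of ANCOVA over a change-score test is a secondary matter and depends on r. A plain two-sample t-test on change would already remove the defect.

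**What to change.** Replace the t-test sentence in section 2.8 with wording such as:

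*The primary analysis compares probiotic with placebo on CSMS at the end of the blinded phase by ANCOVA, with treatment and baseline CSMS as terms. The between-group difference is reported with its 95% confidence interval and two-sided p-value. Within-group changes are descriptive only.*

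If ANCOVA is not wanted, a two-sample t-test on change is the minimum. The time point should fall before the further 4 weeks in which all patients receive probiotic (section 2.4). CSMS follows the abstract; section 2.6 lists three primary tools, and that needs its own reconciliation.

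The cost is a change of wording. Section 2.7 places the first evaluation before the allocation envelope is opened, so a baseline value should already be available provided CSMS is recorded there. The correction itself calls for no extra patients, but it makes plain what 60 children can show. At 30 per arm with no dropout, by the normal approximation, the two-sample test on change has 80% power for a difference of √(2/30) × (1.960 + 0.842) = 0.72 SD, and about 49% power for 0.5 SD.

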## Discussion

3

The effect of probiotics on immune function has been a hot topic in allergic diseases in recent years.^[7,8]^ In recent years, it has been widely reported that probiotics can improve the intestinal mucosal immune function of allergic rats and down-regulate the function of TH_2_ cytokines to mediate the TH_1_/ TH_2_ balance, thus preventing the occurrence of food allergy.^[9]^ Animal experiments have revealed that lactic acid bacteria can promote TH_1_ immune response, inhibit TH_2_ immune response, make the body's immune system in a dynamic balance and inhibit the occurrence of allergic reactions. In addition, animal studies have demonstrated that lactic acid bacteria can induce the production of IL-12 and IFN-γ, reduce the production of IL -4, IL-5 and IL-3, promote the immune response of TH_1_ and inhibit the occurrence of allergic reactions. Therefore, prebiotics might have the preventing potential on AR.

Prebiotics are a group of indigestible food ingredients that promote the colonization and growth of probiotics in the intestinal environment.^[10,11]^ Probiotics can also secrete TGF-β and interleukin-10 through TH_3_ cells and Tr1 cells, inhibit the production of Ig E, thus inhibiting the TH_2_ immune response, so as to put the immune system in a dynamic equilibrium state.^[12]^ In recent years, studies have found that infants and young children born after six months of breast-feeding is the protective factors of AR infants and young children breastfed babies than formula-fed infants are less likely to suffer from allergic diseases,^[13]^ one of the reasons is beneficial in breast milk is born yuan oligosaccharides or low poly galactose, after the birth of the baby to play an important role in the development of the immune system.^[14,15]^

The study design described a double-center, randomized, location at the Minda Hospital of Hubei Minzu University and West China Hospital of Sichuan University, which will be focused on the study about probiotics treatment and its effect on AR symptoms.
